**Analysis**

Linear regression model will be used to investigate whether brain structures (cortical thickness and subcortical volumes) differ between children with and without cognitive deficits (presented as standardized beta and 95% CI)

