**Constructing of Structural Covariance Networks (SCN):**

To investigate SCN, Pearson partial correlation analysis will be conducted on the brain hubs. This analysis will be performed separately for groups: children born preterm with cognitive deficits, children born preterm without cognitive deficits, and children born at-term with normal cognitive function.

In the first step, we will calculate correlation coefficients between each pair of regions within the specified volumes for each group. These correlations will be adjusted for potential confounding variables, including age, sex, socioeconomic status (SES). To control for multiple comparisons, FDR correction will be applied when assessing significant structural covariance between each pair of cortical regions.

In the second step, Fisher’s r-to-z transformation will be applied to the significant structural covariance connections to standardize the correlation coefficients.

Finally, we will assess between-group differences in cognitive structural covariance networks using a z-test. Specifically, we will compare the networks of preterm children with cognitive deficits against those of preterm children without cognitive deficits, and against those of term-born children with normal cognitive function.

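### No multiplicity correction is stated for the regional regressions or the between-group z-tests; the only FDR step covers within-group correlations and does not control their error

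*SAP*

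**What the plan says.** The section on constructing structural covariance networks sets out three steps.

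- **First step.** Within each group separately, "we will calculate correlation coefficients between each pair of regions within the specified volumes for each group". The correction belongs here: "FDR correction will be applied when assessing significant structural covariance between each pair of cortical regions". The FDR method and level are not given.
- **Second step.** Fisher's "r-to-z transformation will be applied to the significant structural covariance connections to standardize the correlation coefficients". Only connections that pass the first step go forward. The SAP does not say whether a connection must be significant in either group or in both.
- **Third step.** "Finally, we will assess between-group differences in cognitive structural covariance networks using a z-test". Preterm children with deficits are compared "against those of preterm children without cognitive deficits, and against those of term-born children with normal cognitive function", which makes two comparisons. No correction is mentioned.

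For regional structure, the Analysis section says: "Linear regression model will be used to investigate whether brain structures (cortical thickness and subcortical volumes) differ between children with and without cognitive deficits". The next two sections list two primary and two secondary contrasts. Results are to be given as standardized betas with 95% confidence intervals, and again no correction is mentioned.

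The Outcomes section names three primary and four secondary networks but gives no hub list, testing order or alpha split. Under Hypotheses, only networks with a significant group difference go on to the ASD/ADHD analysis.

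**The concern.** Every hypothesis in the SAP is about a difference between groups: in cortical thickness, in subcortical volume, or in covariance strength. None asks whether a correlation differs from zero within one group, yet that is the only family for which a correction is specified. FDR control over those tests limits errors about that null hypothesis. It says nothing about the null hypothesis that two groups have the same correlation, or the same regional thickness.

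If the plan is followed as written, each regression and each z-test is judged on its nominal p-value. The chance of reporting at least one spurious regional difference or altered network then grows with the number of tests. The SAP states that registration precedes analysis. A correction rule left open at that stage would have to be chosen after p-values are visible. Chance differences would also decide which networks are examined against behavioural scores.

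**Working it through.** The SAP gives no alpha, power or expected number of findings, so there is no stated figure to reproduce.

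**Inputs from the SAP.** 3 primary and 4 secondary networks (Outcomes); 2 primary and 2 secondary regression contrasts (Primary analysis, Secondary analysis); 2 between-group network comparisons (network section).

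**Assumptions.** Two-sided 0.05 per test, all true differences zero, independent tests. The number of regions or hubs is not stated; a range is shown.

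**Formulas.** Expected false positives = m x 0.05. Chance of at least one = 1 - 0.95^m.

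| Tests | m | Expected | Chance of at least one |
|---|---|---|---|
| 3 primary networks x 2 contrasts | 6 | 0.30 | 0.265 |
| 7 networks x 2 contrasts | 14 | 0.70 | 0.512 |
| 7 networks x 4 regression contrasts | 28 | 1.40 | 0.762 |
| 20 assumed regions x 2 primary contrasts | 40 | 2.00 | 0.872 |

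If the z-tests are run per connection, h hubs give h(h-1)/2 pairs. Over two comparisons and before any screening:

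- 5 hubs: 10 x 2 = 20 tests, 1.0 expected
- 10 hubs: 45 x 2 = 90 tests, 4.5 expected
- 20 hubs: 190 x 2 = 380 tests, 19 expected

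The expected numbers do not need independence. The chances of at least one do, and positive correlation among brain measures lowers them.

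**Does the within-group FDR screen protect the z-tests?** The three steps were simulated for one comparison with equal true correlations in both groups: Benjamini-Hochberg within each group, then an uncorrected z-test on the surviving connections. Assumed settings were independent connections, 45 or 190 pairs, true r from 0.1 to 0.5, group sizes 50/150, 50/1000 and 100/100, and 1000 runs each.

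- *Significant in either group, r of 0.2 or more:* at least one false difference in about 85% to 100% of runs, with about 2 of 45 or 8 to 10 of 190 connections falsely different.
- *Significant in either group, r = 0.1:* 38% to 100%.
- *Significant in both groups:* from about 0 to 100%, depending on r and group sizes.

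The reason is visible in single settings. With groups of 50 and 150, r = 0.3 and 45 pairs, the either-group screen passes 43.9 connections on average. At 5% each that gives 43.9 x 0.05 = 2.2 false differences, and the simulation gave 2.2. The screen removes almost nothing. With weak correlations it removes a great deal, but it keeps the connections whose sample correlation is large by chance in one group. With groups of 100 and 100, r = 0.1 and 190 pairs, 3.19 survive on average and 1.46 of them test as different, a rate of 1.46 / 3.19 = 0.46.

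**Would correcting only the survivors be enough?** Benjamini-Hochberg on the surviving connections gave a 0.00 to 0.07 chance of any false difference when r was 0.3 or more, but up to 0.53 in some settings with r of 0.1 to 0.2, because the screen and the z-test use the same data. Corrected over all pairs, the chance was about 0.05.

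**The case against.** The case for a milder reading has several parts.

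**Size.** A reader might infer that a long list of false findings is certain. The document does not support that. The Outcomes section limits the study to hubs of seven named networks, so a whole-atlas count of tests is not clearly intended. Adding primary and secondary contrasts together merges what the plan keeps apart. The network section ends by speaking of comparing networks, so the z-tests may be few. The 380-test figure is an upper case for 20 assumed hubs, because the plan tests only screened connections. At the low end, six tests give a 27% chance of any false positive. This stands, and it is why a range is reported. In the other direction, the Analysis section speaks of brain structures, which makes region-level testing the more natural reading of the regressions.

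**Misplaced or refused correction.** A reader might also infer that the FDR step is in error, or that the plan rejects correction elsewhere. It does neither. Correcting the screen is legitimate, since it decides which connections go forward, and the SAP is silent about the later tests. Silence still leaves them at nominal level if the text is followed. The primary and secondary labels do not fill the gap, as no testing order or alpha split is attached to them.

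**Behavioural step.** It is tempting to say that the error spreads to the ASD/ADHD results. The SAP presents that step as exploratory. A chance group difference selects which network is looked at; it does not in itself create a false association with behaviour, and no such inflation has been shown.

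**Context.** This is a preregistered observational analysis with named primary networks and contrasts, and its regressions report estimates with confidence intervals. That lowers the stakes but does not supply error control for the group differences.

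**Conclusion.** The concern holds as a gap in error control for the tests that carry the hypotheses. No correction is stated for the regional regressions or the between-group z-tests, and the within-group FDR step does not control the error of either.

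The size cannot be fixed from the document. Under an assumed 0.05 per independent test with no true differences, the chance of at least one false positive is 27% for 6 network-level tests, 51% for 14, and 87% for 40 region-level tests with 20 assumed regions. The lowest of these is about five times the nominal 5% (0.265 / 0.05 = 5.3). Correlated measures would bring these chances down while leaving the expected numbers (0.3, 0.7 and 2.0) unchanged.

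The finding that the screen gives no protection rests on the simulated settings above and on the rule for carrying connections forward, which the SAP leaves open. Under a both-groups rule some settings were conservative, but others were not.

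**What to change.** Before analysis, amend the SAP as follows.

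1. List the hubs, cortical and subcortical, with the network each belongs to. State whether the z-test is done per connection or per network.
2. Regressions: apply Benjamini-Hochberg FDR at q = 0.05 to the p-values across regions in the two primary contrasts, with the primary networks as the confirmatory family and the higher-order networks as a second family. Correct the two secondary contrasts as their own family, or label them exploratory.
3. Network comparisons: apply Benjamini-Hochberg FDR at q = 0.05 to the between-group z-tests over all pre-specified pairs or networks in each of the two comparisons. Do not restrict the family to connections that pass the within-group screen.
4. Call a difference altered, and pass it to the exploratory ASD/ADHD step, only if it survives this correction.

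The cost is SAP wording plus the work of settling the hub list and testing unit, without which no family can be defined. No new data are needed. The downside is that some nominally significant findings will no longer count.

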**Hypotheses**

Children born before 34 weeks with cognitive deficits will show mixed patterns of cortical thickness (i.e., thinner in primary sensory hubs and thicker in higher-order cognitive hubs) and smaller subcortical volumes at 10 years of age compared to both children born before 34 weeks without cognitive deficits and those born at term without cognitive deficits.

We expect higher structural covariance (stronger connection/coordination) in primary sensory networks and lower structural covariance (weaker connection/coordination) in higher-order networks in children born before 34 weeks with cognitive deficits.

We will extract individual structural covariance values only for the networks that show significant differences in the primary analysis and explore their relationship with behavioral outcomes, such as ASD and ADHD symptoms at 12 years of age.

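### Connections are screened by within-group significance before the between-group z-test, and the plan does not say in which group; some readings remove most of the hypothesised weaker connections

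*SAP*

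**What the plan says.** The section on constructing structural covariance networks sets out three steps.

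1. Partial correlations are computed group by group: "This analysis will be performed separately for groups: children born preterm with cognitive deficits, children born preterm without cognitive deficits, and children born at-term". The last of these groups is limited to children whose cognition is normal. Within each group, "FDR correction will be applied when assessing significant structural covariance between each pair of cortical regions".
2. The Fisher r-to-z "transformation will be applied to the significant structural covariance connections to standardize the correlation coefficients".
3. Then "we will assess between-group differences in cognitive structural covariance networks using a z-test". The contrasts are the preterm deficit group against the preterm group without deficits, and against the term group.

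The Hypotheses section predicts both directions. It says "We expect higher structural covariance (stronger connection/coordination) in primary sensory networks" and also "lower structural covariance (weaker connection/coordination) in higher-order networks in children born before 34 weeks with cognitive deficits". It also limits the later behavioural analysis to networks that differ significantly.

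The SAP does not give a rule for a connection that is significant in one group only, the FDR level, the group sizes, or any multiplicity control for the between-group tests.

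**The concern.** A z-test of one connection between two groups needs a Fisher z from each. Step 2 provides one only for significant connections, and significance is judged separately in each group. A connection that has weakened toward zero in the deficit group is the one most likely to fail step 1 there. If failing there excludes it, the filter works against the second half of the hypothesis.

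Significance in one group and not in another is also no evidence of a difference, yet here it may decide which differences get tested. It depends on group size as well as on the correlation.

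Three things are at stake: power for the predicted reductions, the direction of whatever is found, and the choice of networks for the ASD and ADHD analysis. An open rule could also be settled after the data have been seen.

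**Working it through.** The plan states no power, group size or error level for this step, so there is no figure to reproduce. The check compares readings of the filter.

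**Inputs.** From the SAP: the three-step sequence, and adjustment for age, sex and SES. Taken as k = 5 covariates, because the Covariates section lists three SES items. Assumed: group sizes, true correlations, 45 independent connections, Benjamini-Hochberg at 5% within group, and a two-sided 5% z-test.

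**Formulas.** z = atanh(r), with SE = 1/√(n − k − 3) = 1/√(n − 8). Between groups, Z = (z₁ − z₂)/√(SE₁² + SE₂²).

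**Hand check, 50 v 200, with an uncorrected 5% filter (more lenient than FDR).**
- Deficit-group SE = 1/√42 = 0.154. To pass, z must reach 1.96 × 0.154 = 0.302, so r must reach about 0.29.
- SE of the difference = √(1/42 + 1/192) = 0.170. A significant reduction needs a further 1.96 × 0.170 = 0.334.
- The comparison-group z must then be at least 0.302 + 0.334 = 0.636, or r of about 0.56.
- With true r of 0.1 v 0.4 and no filter, the expected Z is (0.424 − 0.100)/0.170 = 1.90, and power is Φ(1.90 − 1.96), about 47%.

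**Simulated power for a weaker connection.** The deficit-group rule gives the same figures as the both-groups rule, to rounding.

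| n deficit / comparison | True r deficit / comparison | No filter | Both groups | Either group |
|---|---|---|---|---|
| 50 / 200 | 0.1 / 0.4 | 47% | 0.01% | 47% |
| 100 / 100 | 0.1 / 0.4 | 59% | 0.05% | 59% |
| 80 / 300 | 0.2 / 0.5 | 75% | 4% | 75% |
| 80 / 300, one fifth of connections weak, rest at 0.5 | 0.2 / 0.5 | 75% | 15% | 75% |
| 80 / 300 | 0.3 / 0.6 | 83% | 53% | 83% |
| 80 / 300 | 0.4 / 0.6 | 53% | 48% | 53% |
| 150 / 400 | 0.3 / 0.5 | 69% | 64% | 69% |

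In the first row the connection survives step 1 in only 0.6% of cases. The second row shows that the power loss does not need unequal groups.

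A separate calculation replaced FDR by a fixed 5% filter per connection, with true r of 0.1 v 0.5. Under the strict rules, power fell from 0.63 to 0.006 (40 v 150), 0.92 to 0.07 (80 v 250) and 1.00 to 0.22 (150 v 400). Under an either-group rule it did not change.

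**Direction when nothing differs (true r = 0.2 in both groups, 50 v 200).**
- Both groups: about 5% of connections survive, with a mean deficit-group r of 0.46. Of the survivors, 20% are falsely called stronger and well under 0.1% falsely weaker.
- Deficit group only: 33% of survivors are falsely called stronger.
- Either group: about 5.7% of survivors are falsely called different, split roughly evenly between directions.

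**The case against.** The strongest reply is that the SAP never says a connection must be significant in both groups. Carrying forward any connection significant in either group is workable, because its correlation exists in the other group and can be transformed too. Under that reading, power for weaker connections is intact. This stands. A reader might infer that the plan cannot detect weaker connections at all, but the text does not support that. Even the strict rules let through a connection that is weaker yet clearly nonzero, as the last two rows of the table show, and the Hypotheses section predicts weaker connections, not absent ones.

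A reader might also infer that the filter manufactures findings of higher covariance. It does not: before a fixed-level test a filter can only remove calls. At equal r = 0.2 and 50 v 200, false calls of stronger fall from 2.5% of all connections to about 1.0% under the both-groups rule. The 20% is a share of the few survivors. At equal r = 0.4 that share is about 3%. With equal group sizes (150 v 150, r = 0.2) the both-groups rule is symmetric, at 0.08% of all connections in each direction.

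Finally, a smaller deficit group is plausible from the definition of deficit by distance below the control mean, but the SAP gives no group sizes.

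What survives the reply is the undefined rule and its consequences under two of its three readings. The either-group rule is not free either. It can cost power for stronger connections: 0.58 to 0.34 for r of 0.4 v 0.0 at 40 v 150, with a 0.005 filter per connection.

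**Conclusion.** The concern holds in conditional form. The plan selects connections by within-group significance, on the same data, before the group comparison, and leaves the selecting group undefined.

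- If significance is required in both groups or in the deficit group, many or most of the hypothesised weaker connections can be lost. The loss is greatest when the deficit-group correlation is near zero relative to that group's size, and small (69% to 64%) when it is not.
- If the deficit group is also the smaller one, the surviving connections have inflated correlations and lean toward stronger in that group.
- If significance in either group is enough, power for weaker connections is kept and only slight error inflation among the selected connections remains.

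All magnitudes rest on assumed group sizes, correlations and FDR level, and on independent connections. This should be fixed before analysis. Confidence is moderate, because one plausible reading leaves the hypothesised reductions testable.

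**What to change.** Apply the Fisher transformation to every prespecified connection in every group. Run the between-group test on all of them, using variance 1/(n − k − 3) per group or permutation of group labels. State the FDR level and apply it to the between-group p-values. Report within-group significance for description only.

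This settles every reading and removes the dependence on group size at the selection step. It costs a change of SAP wording and a few lines of code, with no new data. The small downside is a somewhat larger family for the between-group FDR. If a filter is kept, the plan should state an either-group rule and say how the selection is accounted for.
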